### Randomization Procedure

After the baseline (T0) assessment (see later), we will randomly allocate participants to the EMDR or TAU group following a biased coin procedure (29). We want to note that in small clinical trials, simple randomization may lead to substantial imbalance in the relevant confounding factors between groups. The biased coin procedure attempts to balance these confounding factors but it still randomizes the patients and conceals their allocation (30). It has been included in the international guidelines for drug clinical trials (31) adopted by the European Community, Japan, United States FDA, Canada and Switzerland (32).

Specifically, a computer in a central location will allocate the patients as follows: (a) it will randomly allocate the first two patients to one group or the other with p = 0.5, (b) it will allocate the next patients as follows: (b1) if one group already includes at least two more patients than the other group, it will randomly allocate the patient allocated to the smallest group with p = 0.8, (b2) otherwise, it will first simulate that the patient is allocated to EMDR and calculate the sum of the between-group square standardized differences in age, sex and years of education, it will then simulate that the patient is allocated to TAU and recalculate the sum, and finally it will randomly allocate the patient to the group associated to the smallest sum with p = 0.8. Following this procedure, the final groups should be balanced in size and matched in age, sex and years of education. An independent researcher in a central location will control the computer program that will carry all steps of the randomization process.

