## Introduction

Outcomes in patients with schizophrenia spectrum disorders and bipolar disorder have remained suboptimal (1, 2). One factor contributing to this is the high prevalence of psychological trauma and adverse life events in psychosis sufferers, nearly four times the rate in the general population (3). Evidence suggests traumatic life events are an important environmental factor implicated in an increased risk for the onset of a range of psychotic spectrum disorders, including first episode of psychosis (FEP) (4, 5) and affective psychosis in bipolar disorder (6). Additionally, psychological trauma in patients with psychosis is associated with poorer service engagement (7), worse outcomes in the form of longer stays in hospital and more frequent readmissions (8), more severe positive psychotic symptoms (9), and increased suicidal ideation (10).

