The physiopathological mechanisms underlying the link between trauma and psychosis are not fully understood, but appear to be due to a complex interplay of trauma, genetic, epigenetic and environmental factors (4). Furthermore, the prevalence of posttraumatic stress disorder (PTSD) in psychosis was estimated at 12.4% in a meta-analysis of 20 studies (95% CI, 4.0–20.8%) (11). A diagnosis of PTSD in psychosis was associated with poorer social functioning and more severe psychiatric symptoms (12–14). Of particular note is that the experience of suffering a FEP in and of itself can constitute a highly stressful event which triggers symptoms compatible with PTSD: this clinical condition has been defined as post-psychotic post-traumatic syndrome (PPS) (15) and is estimated to occur in 40–80% of all FEP patients (16). A range of issues are potentially traumatic for FEP patients, from the experience of suffering psychotic symptoms, such as auditory hallucinations involving hearing voices, persecutory delusions or disorganized behavior, to the experience of being admitted to a psychiatric unit for the first time. This experience can involve involuntary hospitalizations and/or drug treatment, or other restrictive measures such as mechanical restraints, and is an important risk factor for traumatization (10), and is associated with feelings of anger, sadness, distrust or impotence. The risk of developing PPS following a FEP is increased in patients with prior childhood trauma (17). The presence of PPS is associated with an increased severity in psychotic symptoms (18) and concomitant clinical depression (19). Trauma hinders adherence to drug treatment (20), which is already particularly difficult in FEP patients in general (21). Thus, PPS has significant consequences at both prognostic and treatment levels (15).

All of this evidence suggests there is an urgent need to go beyond the treatment of psychotic symptoms and integrate trauma-focused psychotherapy into the care plan for FEP patients, especially in the high-risk period following hospitalization.

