### Participants

The study sample will consist of 80 outpatients fulfilling criteria for a diagnosis of Schizophrenia or Schizophrenia Spectrum, Major Depressive Disorder with psychotic symptoms, or Bipolar I Disorder with psychotic symptoms according to DSM-5 criteria, who had never experienced psychotic symptoms prior to the current episode. The diagnosis of all participants will be carried out by physicians with extensive experience in the diagnosis of FEP.

Inclusion criteria are (1) age between 16 and 65 years at the time of first evaluation; (2) have been diagnosed with a first psychotic episode in the last year, with or without pharmacological treatment and/or psychiatric hospitalization; (3) presence of one or more traumatic events causing trauma related symptoms (Impact of Event Scale-Revised, IES-R >0 and Subjective Units of Distress, SUD >5); 4) ability to read and write in Spanish.

Exclusion criteria are: (1) acute suicidality; (2) presence of organic brain diseases; (3) previous trauma-focused therapy in the past 2 years.

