
## Limitations

One limitation of this study is the inclusion of both affective and non-affective FEP, as well as comorbid substance use disorders, leading to a more heterogeneous sample. These inclusion criteria were decided on to ensure the study was carried out on a representative real-world population. We suggest this limitation can be addressed by matching the samples in both arms. Additionally, the main underlying clinical variable common to all patients is the presence of comorbid psychological trauma. Another potential source of bias is the lack of control regarding pharmacological treatment. To partly overcome this limitation, a ‘pharmacological treatment’ variable will be included and, to the extent it is possible, patients in the study should not have their drug therapy altered once they are stabilized. As our unit has extensive experience in treating FEP patients and uses standardized treatment protocols, this will also help limit this as a potential source of bias.

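### The biased coin balances age, sex and education but no trauma score, so trauma burden, which the protocol associates with readmission and measures before allocation, is balanced no better than by simple randomization

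*Protocol article*

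**What the plan says.** The Randomization Procedure section gives its reason for the coin: "in small clinical trials, simple randomization may lead to substantial imbalance in the relevant confounding factors between groups". Once the first two patients are allocated, and whenever the arms differ by fewer than two patients, the program tries the new patient in each arm. For each trial placement it will "calculate the sum of the between-group square standardized differences in age, sex and years of education", and then "it will randomly allocate the patient to the group associated to the smallest sum with p = 0.8". The promised result is that "the final groups should be balanced in size and matched in age, sex and years of education". Allocation follows the T0 assessment, and Table 1 lists IES-R, CTQ and SUD at enrolment.

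On trauma and outcome, the Introduction associates psychological trauma in psychosis with "worse outcomes in the form of longer stays in hospital and more frequent readmissions (8", and says that trauma hinders adherence to drug treatment. It adds: "The risk of developing PPS following a FEP is increased in patients with prior childhood trauma (17".

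On entry, the Participants section asks for one or more "traumatic events causing trauma related symptoms (Impact of Event Scale-Revised, IES-R >0", together with SUD above 5. The Limitations section deals with diagnostic and substance-use heterogeneity by matching the arms, and adds that "the main underlying clinical variable common to all patients is the presence of comorbid psychological trauma".

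On analysis, the Statistical Analysis section gives a chi-square test for categorical and main clinical variables. It allows statistically significant variables to be used as covariates in a regression concerned with the size of the effect and predictors of functioning. The Computation of Sample Size section names relapse as the main variable and refers to a Cox regression.

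**The concern.** The coin exists to protect a small trial against imbalance in relevant confounders, but the three factors it uses are demographic, and the article argues no link between any of them and relapse. The factor it does associate with readmission and adherence is trauma, which is left out of the sum although it is already measured when the coin is tossed.

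Eligibility does not make patients alike in this respect. SUD above 5, on a 0 to 10 scale, is a floor on current distress. IES-R total may still lie anywhere above 0 on a 0 to 88 scale, and CTQ severity may run from minimal to extreme. That trauma is present in every patient does not mean that its amount is equal between arms.

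If one arm enters with a heavier trauma burden, and burden is prognostic, part of the relapse difference in the trial actually run would be credited to, or held against, EMDR.

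**Working it through.** The protocol gives no figure for the balance it expects, so there is no stated figure to reproduce here.

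**Inputs from the protocol.** N = 80, 40 per arm; first two patients at p = 0.5; smaller arm favoured at p = 0.8 when the sizes differ by two or more; otherwise the arm with the smaller sum favoured at p = 0.8; terms in the sum are age, sex and years of education.

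**Assumptions.** Continuous covariates normal, sex 50/50, covariates independent. A second simulation with two trauma scores assumed a CTQ-IES-R correlation of 0.3. Each simulation used 3000 trials.

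**Step 1: expected imbalance without balancing.** For a covariate unrelated to the allocation terms, the standardized difference has SD sqrt(1/40 + 1/40) = sqrt(2/40) = 0.224. Under normality, P(|d| > 0.3) = P(|Z| > 0.3/0.224) = P(|Z| > 1.34), about 18%.

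**Step 2: simulation of the coin as written and with trauma added.**

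| Quantity | Trauma outside the sum | One trauma score in the sum | Two trauma scores in the sum |
|---|---|---|---|
| SD of trauma difference | 0.224 (0.224 and 0.226 in the two-score simulation) | 0.091 | 0.100 and 0.099 |
| P(difference > 0.2 SD) | 37% | 3.6% | not computed |
| P(difference > 0.3 SD) | 18.2% (18.4% and 19.3%) | 0.4% | 0.7% and 0.6% |
| 95th percentile | 0.44 | 0.18 | not computed |
| SD of age difference | 0.080 | 0.090 | 0.09-0.10 for age, sex and education |

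The first column agrees with Step 1: the coin gives an unlisted factor no protection. The mean simulated trauma difference was 0.003, so the allocation favours neither arm on average. Age, which is in the sum, exceeded 0.3 SD in 0.3% of trials.

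**Step 3: what a 0.3 SD imbalance could do to relapse.** The documents give no hazard ratio for trauma, so a range is assumed. The approximate shift in the unadjusted log hazard ratio is d × ln(HR per SD).

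- HR 1.3 per SD: 0.3 × ln 1.3 = 0.079, a factor of 1.08
- HR 1.5 per SD: 0.3 × ln 1.5 = 0.122, a factor of 1.13
- HR 1.8 per SD: 0.3 × ln 1.8 = 0.176, a factor of 1.19

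**Step 4: would the stated covariate rule catch it?** If statistical significance there means a baseline difference between arms, p < 0.05 needs |d| of about 1.96 × 0.224 = 0.44. Differences of 0.2 to 0.4 SD would then not trigger adjustment.

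**The case against.** The strongest reply is that 0.224 is what any unlisted covariate shows in any 1:1 trial of 80. The same could be said of diagnosis, substance use or centre. Ordinary standard errors already allow for chance imbalance, and the coin delivers the matching it promises. This stands to the extent that no systematic bias is present and the unadjusted comparison is valid on average. What remains is that trauma is the factor the article itself associates with readmission, and that it is available at no cost when allocation is made.

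Several stronger readings are tempting and are not supported:

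- *That the article shows graded trauma severity to predict relapse.* It speaks of having trauma, prior childhood trauma or PPS. It gives no dose-response among patients who all have trauma, so the hazard ratios per SD are assumptions.
- *That entry leaves distress unrestricted.* SUD above 5 is a floor.
- *That the relapse result would be overturned.* Even if all 72 patients in the sample-size calculation relapsed, the standard error of the log hazard ratio would be about 2/sqrt(72) = 0.24, so the middle shift of 0.122 is about half a standard error. The 0.3 SD imbalance behind it is exceeded in only about 18% of trials.
- *That the trauma results suffer equally.* IES-R, DES and SDQ-20 are repeated at T1 and T2, and the Study Aim section speaks of change from baseline, which would remove much of a baseline difference. The repeated-measures model is, however, named only for functionality and quality of life.
- *That omitting the covariate necessarily loses precision.* In Cox or logistic models, adjustment does not generally shrink the standard error of the treatment coefficient.

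It can also be said that covariates belong in an analysis plan that is not shown. Failure to list them is indeed no finding. What can be criticized is the rule the article does state, which is optional and driven by significance.

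**Conclusion.** The point holds as a worthwhile, inexpensive improvement to a stated rule. The coin is justified by relevant confounders but leaves out the one the article argues for. A trauma score is therefore balanced only as well as by simple randomization: SD about 0.22, with about 18% of trials beyond 0.3 SD, against 0.09-0.10 and under 1% if it is included. These figures rest on N = 80 and the simulation assumptions above.

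The consequence is possible distortion of the relapse comparison in the particular trial run, about 8-19% in the hazard ratio at 0.3 SD. That range depends wholly on the assumed 1.3-1.8 per SD; if trauma burden above the entry floor is not prognostic, the distortion disappears. A reader might infer that the trial is biased, but the imbalance has mean zero and the documents do not support that.

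**What to change.** - **Allocation.** Add one or two baseline trauma scores, IES-R total and CTQ, as further terms in step (b2) of the Randomization Procedure.
- **Analysis.** Pre-specify one baseline trauma score, together with age, sex and years of education, as covariates in the relapse model, in place of choosing covariates by significance. A chi-square test cannot carry covariates, so the relapse comparison would have to be a regression, such as the Cox model already named under Computation of Sample Size.
- **If allocation has begun.** Leave the coin unchanged and make only the covariate change, before outcome data are seen by arm.

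**Cost.** One or two terms in the central program and a sentence in the analysis text; no new data or visits. Balance on age, sex and education weakens slightly, from an SD of about 0.08 to 0.09-0.10.

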### Computation of Sample Size

The study aims to assess the relative efficacy of an EMDR intervention protocol for patients with FEP versus TAU mainly in terms of stabilization and clinical improvement, reduction of anxious, depressive, somatic and/or psychotic symptoms, among others. For this reason, the main variable used is the number of clinical relapses after the intervention, with a follow-up of up to 12 months. Using previous studies as a basis (33), the sample size has been calculated based on a survival analysis with the statistical package “powerSurvEpi” for R, (http://www.r-project.org/) using an alpha = 0.005 instead of 0.05 to allow correction for multiple comparisons. The number of patients required to detect a hazard ratio = 2 in a Cox regression with a statistical power of 80% and alpha = 0.005 is n = 36 per intervention group (two groups, total n = 72). According to Chambless and Hollon (29), a sample of this size should show clinically relevant differences. Assuming a loss percentage of approximately 10–15% of the patients in the study, it would be necessary to recruit approximately 80 patients, 40 for each branch of intervention.

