### Hypotheses

1. Patients in the EMDR group will show fewer relapses compared to the control group after therapy (T1) and at the 12-month follow-up visit (T2).2. Patients in the EMDR group will show fewer psychiatric and trauma-related symptoms compared to the control group after therapy (T1) and at the 12-months follow-up visit (T2).3. Patients in the EMDR group will improve their functional capacity in comparison to the control group at evaluations after therapy (T1) and at the 12-months follow-up visit (T2).4. Patients in the EMDR group will show a better adherence to pharmacological treatment in relation to the control group after therapy (T1) and at the 12-month follow-up visit (T2).

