### Dropouts and Follow-Up

Any patient who is admitted to hospital following a clinical relapse during the 5-month intervention period will be considered to be dropout and will be excluded from the trial. In the case of relapse during follow-up, patients will be removed from the study and relapse-related factors will be collected for subsequent analysis.

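### The main variable is a number of relapses after therapy, but removal at a follow-up relapse caps it at one per patient, so a per-patient count cannot be observed

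*Protocol article*

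**What the plan says.** All references are to the protocol article.

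- **Computation of Sample Size** states that "the main variable used is the number of clinical relapses after the intervention, with a follow-up of up to 12 months". The next sentences say that "the sample size has been calculated based on a survival analysis with the statistical package", namely powerSurvEpi, for a hazard ratio of 2 in a Cox regression with 80% power and alpha 0.005, giving 36 patients per group.
- **Hypotheses**, item 1, expects fewer relapses under EMDR than under control, both at T1 and at T2.
- **Dropouts and Follow-Up** has two rules. The rule for the intervention covers "Any patient who is admitted to hospital following a clinical relapse during the 5-month intervention period"; it states that such a person "will be considered to be dropout and will be excluded from the trial". The rule for the period after it reads: "In the case of relapse during follow-up, patients will be removed from the study and relapse-related factors will be collected for subsequent analysis".
- **Statistical Analysis** names a chi-square test for categorical and main clinical variables, an intention-to-treat main analysis, and last observation carried forward for patients lost to follow-up. No model for counts or recurrent events is named.

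**The concern.** The main variable is worded as a count over the period after therapy. In that same period the removal rule ends a patient's participation at a relapse. The only further data mentioned are factors related to that relapse; nothing says that later relapses are recorded. A patient with one post-therapy relapse and a patient with three would then look the same.

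The rule governs what is collected, so no analysis plan could repair this afterwards. The trial could support a statement about the proportion of patients with a first relapse after therapy, or the time to it. It could not support one about how many relapses patients had. If last observation carried forward were applied to the count of a removed patient, it would carry a 1 to T2 as though nothing further had happened.

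**Working it through.** **1. What each rule allows a patient to contribute**

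| Period | Event | Consequence in the text | Relapses that can be counted |
|---|---|---|---|
| 5-month intervention | Relapse without admission | None stated | No cap stated |
| 5-month intervention | Relapse with admission | Dropout, excluded | As written, none |
| Follow-up | Relapse | Removed from the study | At most one |

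The main variable refers to the time after the intervention, so the third row governs it: 0 or 1 per patient.

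**2. The plan's own figure**

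The plan states no relapse rate or count that could be reproduced. Its only related figure is 36 per group (72 in total). Schoenfeld's formula, with two-sided alpha 0.005, 80% power and 1:1 allocation, gives

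events = (2.807 + 0.842)² / (0.25 × (ln 2)²) = 13.31 / 0.1201 ≈ 111.

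Seventy-two patients supply at most 72 first relapses, so the figure does not reproduce. That is a separate problem. The sizing matters here only because a Cox hazard ratio, as usually applied, concerns time to a first event and needs no repeat relapses.

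**3. Share of relapses that would go unrecorded**

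Assumptions, none from the document: constant first-relapse hazard h; 12-month first-relapse risk R of 20–50%; hazard after a first relapse m·h with m = 1 or 2; a window of 12 − 5 = 7 months, which takes T2 as 12 months from baseline.

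- h = −ln(1 − R)/12 and H = 7h
- probability of a first relapse in the window: p = 1 − exp(−H)
- expected further relapses per patient: m(H − p)
- share lost = m(H − p) / [p + m(H − p)]

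| R | H | p | Lost, m = 1 | Lost, m = 2 |
|---|---|---|---|---|
| 20% | 0.130 | 0.122 | 6% | 12% |
| 30% | 0.208 | 0.188 | 10% | 18% |
| 40% | 0.298 | 0.258 | 14% | 24% |
| 50% | 0.404 | 0.333 | 18% | 30% |

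Over a full 12 months the same formulas give 10%, 16%, 22% and 28% for m = 1, and 19%, 27%, 36% and 44% for m = 2.

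**4. Effect on a between-arm ratio**

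Take a true rate ratio of 2 (TAU to EMDR), constant rates, and a TAU risk R over the counting window. The EMDR risk is then 1 − √(1 − R).

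- R = 20%: 0.200/0.106 = 1.89
- R = 30%: 0.300/0.163 = 1.84
- R = 50%: 0.500/0.293 = 1.71

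If 30% is instead the 12-month risk and only 7 months are counted, the ratio is 0.188/0.099 = 1.90. The hazard ratio for first relapse stays at 2, because it relates first relapses to the time at risk before them.

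**The case against.** The strongest reply is that the sample-size section already points to first relapse. It uses survival analysis, a hazard ratio and Cox regression; the analysis section names a chi-square test; neither needs repeat relapses. The number of relapses can be read as relapse events per arm, which after the cap equals the number of patients who relapse. Repeat relapse is not itself a hypothesis of the trial. Much of this stands: the planned methods suit a first event, and the mismatch lies in the definition of the main variable and the data collected for it. It does not remove the point, because the text never says first relapse and the later relapses are lost under either reading.

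Three stronger readings are tempting and are not supported:

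- **Every patient leaves at the first relapse.** During the intervention only a relapse with hospital admission leads to removal. Those patients are not capped at one but excluded altogether. That conflicts with the intention-to-treat statement and bears on hypothesis 1 at T1, probably more than the lost repeats do.
- **The cap biases the treatment effect towards no difference.** This is true of a ratio of counts or proportions set against the underlying rate ratio, not of the hazard ratio used for sizing.
- **Counting repeats would rescue the power.** With 36 per arm, a rate ratio of 2, constant rates and TAU risks of 20–50%, approximate power at two-sided alpha 0.005 moves only from 5–17% to 5–25%.

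**Conclusion.** The point holds as a conflict between the main variable and the follow-up removal rule. A per-patient number of relapses after therapy cannot be observed; only whether and when a first one occurs can be.

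The size depends wholly on assumed rates. About 6–30% of relapses would go unrecorded in a 7-month post-therapy window; the top of that range needs both a 50% risk and a doubled later hazard. The 12-month range of 10–44% would apply only if relapses were counted for 12 months after therapy. The attenuation, for example from 2 to about 1.84, concerns counts or proportions only. The calculation treats post-therapy follow-up as a fresh start and ignores unadmitted relapses during therapy, for which the document gives no information.

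The matter is worth correcting before data are lost, since relapses not recorded at the time may be hard to recover. It does not invalidate a first-relapse analysis.

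**What to change.** 1. Reconcile Computation of Sample Size with Dropouts and Follow-Up by defining the main variable as first relapse, or time to first relapse, in line with the Cox sizing.
2. Keep every randomised patient in the relapse analysis, including those admitted during the intervention, as the intention-to-treat statement requires.
3. After a first relapse, go on recording relapse dates and admissions from clinical records to T2. This concerns data collection only and leaves clinical care untouched.
4. Report total relapses per patient as a secondary rate.

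If later relapses will not be recorded, change the sample-size wording to first relapse and limit the conclusions to the proportion with, or the time to, a first relapse. The aim and hypothesis 1 speak only of reducing relapses or of fewer relapses, so they need at most a matching clarification.

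The cost is an amendment, consent wording that covers continued access to records, and a little extra data collection at the centres.

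### The sample-size statement cannot hold: HR = 2 with 80% power at alpha = 0.005 needs about 111 relapses, but the trial has 72 analysable patients who each contribute at most one

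*Protocol article*

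**What the plan says.** The Protocol article, Computation of Sample Size, defines the endpoint for sizing: "the main variable used is the number of clinical relapses after the intervention, with a follow-up of up to 12 months". It then says that "the sample size has been calculated based on a survival analysis with the statistical package “powerSurvEpi” for R". The significance level is described separately, as "using an alpha = 0.005 instead of 0.05 to allow correction for multiple comparisons". The target is given as "The number of patients required to detect a hazard ratio = 2 in a Cox regression", and the result as "statistical power of 80% and alpha = 0.005 is n = 36 per intervention group (two groups, total n = 72". Losses are added last, with the allowance given as "Assuming a loss percentage of approximately 10–15% of the patients in the study". From this the section concludes that "it would be necessary to recruit approximately 80 patients, 40 for each branch of intervention". The section cites previous studies as its basis. It prints no relapse probability, no number of events and no sidedness for alpha.

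Two other sections bear on the count.

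- Dropouts and Follow-Up: a patient admitted to hospital after a relapse during the 5-month intervention "will be considered to be dropout and will be excluded from the trial". A patient who relapses during follow-up is removed from the study.
- Statistical Analysis: a chi-square test is named for group differences in categorical and principal clinical variables. No Cox model is mentioned.

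**The concern.** The power of a Cox or log-rank comparison is set by the number of events, not the number of patients. A hazard ratio of 2 is a large effect, but alpha = 0.005 is a demanding level, and the two together call for more events than the stated number of patients could produce.

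This paragraph is the only quantitative justification of the trial's size, and relapse is its main outcome. If the 80% figure stands, a non-significant relapse result may be read as adequately powered evidence that EMDR does not reduce relapse. The Discussion's description of the trial as a large RCT would encourage that reading.

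**Working it through.** **Inputs** (Computation of Sample Size): HR = 2, power 80%, alpha = 0.005, two equal groups, n = 72 analysable, 80 recruited, loss 10–15%. Sidedness is not stated, so both versions are shown.

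**Events per patient.** Removal at relapse during follow-up allows at most one post-intervention relapse per patient. A relapse leading to admission during the intervention takes the patient out altogether. The number of patients is therefore an upper limit on the number of events.

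**Formulas**, 1:1 allocation, with z for alpha and 0.842 for 80% power:

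- Schoenfeld: d = 4(z + 0.842)² / (ln HR)²
- Freedman: d = (z + 0.842)² × ((HR + 1)/(HR − 1))² = 9(z + 0.842)² at HR = 2

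**Attempt to reproduce n = 72**

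| Alpha | z | Schoenfeld events | Freedman events |
|---|---|---|---|
| 0.005 two-sided | 2.807 | 110.8 | 119.8 |
| 0.005 one-sided | 2.576 | 97.2 | 105.1 |
| 0.05 two-sided | 1.960 | 65.3 | 70.6 |
| 0.05 one-sided | 1.645 | 51.5 | 55.6 |

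Nothing at 0.005 gives 72 or fewer, even with every patient relapsing. The smallest count, 97.2, also exceeds 80.

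At 0.05 the figure can be reached. With Freedman, two-sided and every patient relapsing, 70.6 / 2 = 35.3, which rounds up to 36 per group. This is not the only route. Other combinations at 0.05 give 72 patients with a suitable relapse probability:

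- Schoenfeld two-sided: 65.3 / 72 = 0.91
- Freedman one-sided: 55.6 / 72 = 0.77
- Schoenfeld one-sided: 51.5 / 72 = 0.71

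**Upper limit on power at 0.005.** Power = Φ(√d × ln 2 / 2 − z), two-sided z = 2.807:

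- d = 72: Φ(2.941 − 2.807) = 55% (Freedman analogue Φ(√d/3 − z): 51%)
- d = 80: Φ(3.100 − 2.807) = 61.5% (Freedman: 57%)
- One-sided (z = 2.576): 64% and 70% (Freedman: 60% and 66%)

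**Illustration under assumed relapse risks.** The document gives no risk, so 30% and 50% of 72 patients are assumed. The detectable HR at 80% power is exp(2 × (2.807 + 0.842)/√d).

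| Relapsing (assumed) | Events | Power, two-sided 0.005 | Detectable HR |
|---|---|---|---|
| 30% | 22 | Φ(1.626 − 2.807) = 12% | 4.7 |
| 50% | 36 | Φ(2.079 − 2.807) = 23% | 3.4 |

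**Attrition.** 72/0.90 = 80, so the recruitment target works at 10% loss. At 15%, 72/0.85 = 84.7, so 85 would be needed; 80 × 0.85 = 68 remain, not 72.

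**The case against.** The strongest defence is that a journal article condenses its protocol. The section cites previous studies, and an input that is not printed may still have been used. It would therefore be wrong to infer that no relapse probability entered the calculation. That stands, but it does not rescue the figure: the required events exceed the number of patients at every relapse probability up to 1.

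A second defence is that the endpoint is worded as a number of relapses, which could include repeat events. The stated method is a Cox hazard ratio, however, and patients are removed at relapse, so repeats cannot fill the gap.

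Three stronger readings are tempting, and the documents do not support them.

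- **That an event count at 0.05 was reported as a patient count at 0.005.** The Freedman match is suggestive, but other routes at 0.05 also lead to 72. The origin remains an inference.
- **That true power is a small fraction of 80%.** Without an assumed relapse risk, the documents support only the upper limits of about 55% and 61.5%. The 12–23% range depends on the assumed risks.
- **That the intervention-period exclusion cuts the trial to about 13 events.** With an assumed 40% 12-month risk under usual treatment, a true HR of 0.5 and 40 per arm, that count also requires every relapse in months 0–5 to lead to admission and a 12-month clock from baseline. If follow-up instead runs 12 months after the intervention, as the label of T2 in Tables 2–4 could suggest, the count is about 21.

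It is also fair to say that the shortfall at 15% loss is small and that the section's wording is approximate.

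**Conclusion.** The point holds. The stated sample size, hazard ratio, alpha and power cannot all be true. The incompatibility needs no outside figure, and it survives the choice of formula and of sidedness. It rests on equal allocation and at most one counted relapse per patient, both of which follow from the document.

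The shortfall is at least 97.2 − 80 = 17 events under the most lenient version. It is about 111 − 72 = 39 under the usual two-sided Schoenfeld calculation for the analysable sample, even if every patient relapsed. How far actual power falls below the 55–61.5% limits cannot be settled without a relapse probability, the events lost to the intervention-period exclusion, and a decision on the test.

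A reader might also infer that relapse should simply be tested once at 0.05. The documents do not make that a correction. The stricter alpha is a stated safeguard against multiple comparisons, and Hypothesis 1 claims fewer relapses at both T1 and T2. Changing the level is a design choice for the investigators. Nor would it restore the claim at the assumed risks: with 22–36 events, power at two-sided 0.05 is Φ(1.626 − 1.960) = 37% to Φ(2.079 − 1.960) = 55%.

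The attrition shortfall at 15% is minor.

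**What to change.** Withdraw the 80% power claim and rewrite Computation of Sample Size to state:

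1. the assumed relapse probability in each arm and its source;
2. the number of relapses expected from 80 recruited patients, after losses and after the exclusions in Dropouts and Follow-Up;
3. the alpha and sidedness used for relapse;
4. the power for HR = 2, and the hazard ratio detectable with 80% power, at that event count.

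Reconcile the Cox calculation with Statistical Analysis, so that the power quoted belongs to the test that will be used for relapse. Report the relapse hazard ratio with its 95% confidence interval, so that a null result is read by its precision. In the same edit, align the loss allowance with the recruitment target: 80 covers 10% loss but not 15%.

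The cost is a rewritten paragraph and a consistent line in Statistical Analysis. No extra patients are needed. The stated power will be much less favourable.
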